### Study sample and recruitment

Inclusion and exclusion criteria for the current study are summarized in Table 1.

**Table 1 Tab1:** Eligibility criteria

Inclusion criteria	Exclusion criteria
Patients perceive PACS symptoms	High need for care as classified according to German health care levels (>/= 2)
Patients who have the necessary prerequisites to participate in the online-screening as well as in telephone or video-conferences with their personal pilots	No mobile device (smartphone, laptop, tablet, or computer) and/or internet connection, no telephone or video conference system, or no sufficient technology literacy to make use of it
Registered in Bavaria, Germany	Occupancy in the healthcare or welfare system or laboratory
Age between 18 and 60 years	PACS treatment or therapy (including rehabilitation)
Willingness to participate in outpatient or (partially) inpatient therapy	Acute COVID-19 infection less than 4 weeks ago
Sufficient German skills	Insufficient literacy of the German language to participate in data collection and digital treatment options Severely limited cognitive, hearing and vision abilities, as linguistic components of the digital offers and auditory stimuli must be understood
Physical conditions that allow participants to take part in the digital intervention exercises	Severely limited physical conditions such as bedriddenness
Patients that do not receive PACS treatment so far	

Patients will be asked to participate in the study after they were positively screened in the initial online screening. The *recruitment* will be carried out in two ways: Firstly, patients are sought to be reached via multiplicators. These include general practitioners (GPs) and specialized primary care physicians, post-COVID outpatient clinics and administrative institutions. GPs and specialists will be informed in advance about the possibility of the screening based on an existing address database. It is assumed that approximately every tenth physician will identify patients as potential candidates and can refer approximately one patient to the study. If 1000 multiplicators are contacted, about 100 potential participants can be screened.

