#### 1. Low-threshold online screening tool

To establish a quick and easy-to-use screening tool for patients who assume that their symptoms are due to PACS, a low-threshold online screening instrument was developed and will be evaluated during the duration of the project (see Additional file 1﻿: Appendix). The screening is of subjective nature. It consists of 14 questions that assess symptoms related to PACS. In addition, the screening includes further questions that assess the diagnosis and timeline of acute COVID-19, limitations in daily life and previous treatment measures to reflect the inclusion and exclusion criteria. Furthermore, demographic questions are asked about age, sex, and place of residence.

If the responses indicate the likelihood of PACS, and that the participants meet the inclusion criteria (Table 1), participants are asked to provide their contact details so that they can be contacted by the personal pilot and take part in the study. In this case, patients are randomly assigned to either the intervention group (IG) or the active control group (ACG). If a randomized approach is not possible (e.g., if it is not possible for a patient to take part in the three-day assessment program), they will not be randomly assigned but marked for the statistical analyses. If there is no indication of a PACS in the screening tool, participants will be directly informed of this, and advised to contact their GP for further clarification and support. In the scope of the project, the online screening will be validated with the results of the assessment program to ensure that the screening can reliably identify patients suffering from PACS and inform future interventions. In detail, the results from the assessment will serve as a gold standard for the validation of the online screening. That is, after the assessment, practitioners will be asked to decide to what extent patients are indeed affected by PACS. This decision will be used to be able to determine the sensitivity for the online screening. In case of an acceptable match between the decision of the practitioners and the online screening, the online screening can be used as a starting point for appropriate treatment of patients and Hypothesis 1 that a short screening is able to detect the presence of PACS will be validated.

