### Evaluation concept

A longitudinal randomized control trial design is used in this project with a three-group pretest–posttest procedure. Whereas the CompG will be recruited with different links via online invitations (e.g., via social media campaigns), the IG and the ACG are recruited with another separate link. After agreeing to take part in the study, participants will be randomized by throwing a dice. Patients for whom a 1 or 2 was rolled are placed in the IG and patients for whom a 3–6 was rolled are placed in the ACG. If a randomization cannot be realized (e.g., because they cannot take part in the stationary assessment due to organizational limitations), patients will be allocated to the ACG but will be marked for statistical analyses. Methodically, a propensity score matching will be used between the IG and the CompG to ensure the comparability of these groups (i.e., participants will statistically be matched by various person-related criteria such as age and sex). All groups are repeatedly interviewed with similar instruments in each group (see Table 1). Time points of measurement are the screening (T1), prior to the assessment in the IG and a comparable time point in the ACG (T2), after the assessment in the IG and at a comparable time point in the ACG (T3). Then approximately 6 weeks after T3 and after symptom-specific digital interventions, a further measurement will take place (T4). Another 6 weeks later a follow-up measurement will take place (T5). A last measurement time point (T6) will be conducted 6 months later with some selected participants. All time points of measurement are included in the study flow chart (Fig. 3).

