### Statistical analysis

#### Sample size planning

With an alpha error of 0.05 and a power of 68%, a sample of *N* = 132 (*n* = 66 in the IG and *n* = 66 in the ACG) is required to be able to demonstrate an effect of *d* = 0.15. The evaluation will be conducted statistically using a Multivariate Analysis of Variance (repeated-measures MANOVA: within-between interaction; power analysis calculated with G*Power). In addition to classical significance tests (*p*-value of a two-sided test below 0.05), the clinical significance will be calculated with effect sizes.

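### T1 is both the symptom-based entry screen and the first listed measurement; name the baseline, adjust for the T1 symptom score instead of treating it as an outcome level, and hold the CompG to the same screen

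*Protocol article*

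**What the plan says.** **Entry.** Study sample and recruitment: "Patients will be asked to participate in the study after they were positively screened in the initial online screening". Of the screening tool, section 1 (Low-threshold online screening tool) says: "It consists of 14 questions that assess symptoms related to PACS". It makes entry conditional: "If the responses indicate the likelihood of PACS, and that the participants meet the inclusion criteria", after which the patient is assigned to IG or ACG. The article gives no numerical cut-off.

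**Measurement.** Evaluation concept describes a three-group pretest-posttest procedure and begins its list of occasions with "Time points of measurement are the screening (T1"). T2 and T3 lie before and after the assessment in the IG, with comparable times in the ACG. T4 follows about 6 weeks after T3, and T5 another 6 weeks later. No symptom criterion is described for T2 to T5. On instruments it says only: "All groups are repeatedly interviewed with similar instruments in each group".

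**Analysis.** Symptom reduction is a primary endpoint, with return to work. Sample size planning names the model: "repeated-measures MANOVA: within-between interaction". Sections 2 and 3 and Type of statistical analysis used repeat MANOVA and repeated-measures ANOVA for Hypotheses 3 and 5, comparing IG, ACG and CompG on how symptoms develop. No adjustment for a baseline symptom score is described.

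**CompG.** It is recruited separately: "Whereas the CompG will be recruited with different links via online invitations". Propensity matching is planned between IG and CompG only; the criteria given as examples are age and sex.

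**The concern.** A score observed only because it passed a threshold is, on average, too high. The next measurement, which has no threshold, falls back even if nothing is done. If T1 opens the outcome profile, part of any later decline is this regression to the mean.

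Three uses of the data are affected differently:

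- **Change within a group.** A decline from T1 could be read as recovery under the pathway (Hypothesis 5), although selection alone would produce some of it.
- **IG or ACG versus CompG.** If the CompG enters without the same symptom gate, it has less of this fall, and the difference looks like benefit.
- **IG versus ACG.** Both arms pass the same gate before randomisation, so the expected fall is equal and cancels. What remains is precision: using the pre-care score as an outcome level rather than a covariate can waste information already collected.

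**Working it through.** **The plan's own figure.** Sample size planning states 68% power, N = 132 (66 per arm), alpha 0.05 two-sided, effect 0.15. For a within-between interaction with noncentrality λ = f²·N·m/(1 − ρ), taking f = 0.15, m = 2 measurements and ρ = 0 gives λ = 0.0225 × 132 × 2 = 5.94 and power 67.7%. The figure is reproduced, but m and ρ are assumptions. Reading the effect as d (f = 0.075) with m = 3 and ρ = 0.7 gives λ = 7.43 and 67.8%. So the stated power does not reveal how many time levels, or which ones, enter the model.

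**Which occasion is the pretest?** The article does not say. Two things point to T1. Pilot contact and the unspecific digital interventions start soon after a positive screen (Study design and setting), so T2 falls after care has begun. T2 and T3 are also defined only for the IG and ACG, so T1 is the only pre-care occasion that three groups could share. This is an inference.

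**Fall without treatment.** Assumptions, since the documents give no values: normal score, share p screens positive, correlation r between T1 and a later score. With z the cut-off, the gated T1 mean lies φ(z)/p above the ungated mean, and the expected fall is (1 − r)·φ(z)/p in ungated SD units.

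| Share positive | φ(z)/p | Fall, r = 0.6 | Fall, r = 0.7 | Fall, r = 0.8 |
|---|---|---|---|---|
| 50% | 0.798 | 0.32 | 0.24 | 0.16 |
| 70% | 0.497 | 0.20 | 0.15 | 0.10 |
| 80% | 0.350 | 0.14 | 0.105 | 0.07 |
| 90% | 0.195 | 0.08 | 0.06 | 0.04 |
| 95% | 0.109 | 0.04 | 0.03 | 0.02 |

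**Randomised contrast.** In simulation, the type I error of the T1-to-T5 group-by-time test stays at 4.3 to 5.3%. There is no bias.

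**CompG contrast, worst case.** Take 66 gated against 66 ungated, unmatched patients from the same population, with no effect. The variance of change is k(1 − r)² + (1 − r²) in the gated group, where k is the T1 variance left after gating, and 2(1 − r) in the ungated group. At p = 0.5 and r = 0.6, k = 0.363, so the standard error is √((0.698 + 0.800)/66) = 0.151 and the standardised shift is 0.319/0.151 = 2.12. The change contrast then rejects in about 56% of trials. Over r = 0.6 to 0.8 the rates are:

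- 50% positive: 31 to 56%
- 80% positive: 10 to 15%
- 90% positive: 6 to 8%
- 95% positive: 5 to 6%

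With T1 as covariate the rate is about 5% throughout. If both groups pass the same gate, the change contrast itself is at about 5%.

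**Precision, separate from the gate.** The variance of change from T1 relative to ANCOVA is 1 + k(1 − r)/(1 + r). Over r = 0.6 to 0.8, ANCOVA cuts the variance by:

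- 50% positive (k = 0.363): 3.9 to 8.3%
- 80% positive (k = 0.583): 6.1 to 12.7%
- 95% positive (k = 0.810): 8.3 to 16.8%

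The gain is larger when the gate is looser, so the gate does not cause the loss.

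**Against the multi-level test.** For an assumed 0.30 SD effect at T4 and T5 with correlation 0.5, the T1-to-T5 interaction has about 54% power, ANCOVA of T5 on T1 about 51%, and ANCOVA of the T4/T5 mean on T1 and T2 about 75%.

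**The case against.** The strongest reply is that the article never says T1 is analysed as an outcome level. It names no pretest, does not say the 14-item screener is the symptom endpoint, and refers to a supplementary file for the measures. Choice of baseline is often left to the analysis plan. That stands, and it makes the point conditional. It does not remove it: the article does fix the occasions and the model, describes no baseline adjustment, and compares three groups whose only shared pre-care occasion is T1.

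Other replies also stand in part:

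- **The time main effect is not the stated effectiveness test.** Correct; the plan asks whether groups differ. The warning about change within a group concerns interpretation.
- **The tool is called low-threshold and is aimed at people who already suspect PACS.** If 90 to 95% pass, the fall is at most about 0.08 SD.
- **Study design and setting says all participants are screened first, and the matching criteria are open-ended.** So a gated or T1-matched CompG is not excluded. But the positive-screen path described in sections 1 and 4 leads to IG, ACG and a pilot, age and sex are the only criteria named, and ACG versus CompG has no matching.

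Stronger readings are tempting. A reader might infer that the main randomised comparison is biased; it is not. A reader might infer that the planned interaction test is inefficient because of the gate; the gate shrinks the loss, and 54% against 51% shows that a multi-level interaction is not clearly worse than ANCOVA of T5 alone. A reader might set the fall against the planned effect of 0.15; that compares a within-group fall with a between-group effect whose scale is uncertain, since 68% is reproduced with f = 0.15.

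**Conclusion.** The point holds in conditional form. T1 is the symptom gate and the first listed measurement, and the stated model adjusts for no baseline. If T1 is used as the first outcome level:

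- A fall without treatment is expected, from 0.02 to 0.04 SD (95% positive) to 0.16 to 0.32 SD (50% positive). This assumes a normal score and a correlation of 0.6 to 0.8; the true size cannot be derived from the article.
- Change from T1 within a group is not evidence of benefit.
- IG versus ACG stays unbiased.
- IG or ACG versus CompG can be biased, but only if the CompG is gated differently. The rejection rates of 31 to 56% need a gate that only half pass and an ungated, unmatched CompG. The documents do not establish either condition.
- Independently of the gate, a simple change-from-T1 contrast has higher variance than ANCOVA: covariate use saves about 4 to 13% at 50 to 80% positive and up to about 17% at 95%.

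This is worth correcting because the remedy is cheap, not because the randomised result is in danger.

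**What to change.** In sections 2 and 3, Sample size planning and Type of statistical analysis used:

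1. Name the baseline occasion for the symptom endpoint.
2. Compare groups on the post-assessment symptom scores, for example T4 and T5 jointly or averaged, with the T1 symptom score as covariate and not as an outcome level. The 75% power shown above also adjusts for T2, so it should not be promised for a model with T1 alone.
3. State that change from T1 within a group will not be read as benefit.
4. Apply the same positive-screen rule to the CompG, and include the T1 symptom score in the matching or in the model for both IG and ACG comparisons with it.

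**Cost.** Mainly wording, plus a covariate that the screening already collects in every randomised patient. Screen-negative CompG volunteers would be lost; how many depends on the cut-off.

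**Limit.** Step 4 reduces confounding from the different recruitment route but does not remove it. If the CompG's true mean were 0.3 SD lower (an assumption), T1-adjusted ANCOVA against an ungated CompG would still reject a true null in 8 to 15% of trials at 80 to 95% positive. CompG results should therefore stay observational in how they are reported.

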**Fig. 3 Fig3:**
[figure not shown]
Flowchart of the study design. *IG* Intervention Group, *ACG* Active Control Group

Patients are invited via primary care physicians, support groups, press releases, and social media. Participants may take part when they show signs of PACS symptoms that last longer than 4 weeks after the acute COVID-19 infection. All participants will first take part in a low-threshold *online screening*. Following the online screening, patients receive direct feedback as to whether they are suitable to take part in the study (i.e., whether there are indicators of risk factors of the presence of PACS). Shortly after the positive screening patients from the IG and ACG receive their first contact with a personal pilot.

Patients from the IG and the ACG will then receive unspecific *digital interventions* (e.g., hygiene recommendations etc.). In the IG, this unspecific digital intervention will be made available to bridge the time to an assessment that takes place in a clinic and in which patients will be assessed by a multiprofessional team of health care professionals. After the assessment, patients in the IG receive digital interventions that aim to meet their individual needs in terms of their physical capacity (i.e., physically very resilient, moderately resilient, barely resilient); patients in the ACG receive digital interventions that are individualized based on the most debilitating symptoms (fatigue, neuro-cognitive symptoms, cardio-respiratory). The digital intervention tools consist of training plans on the one hand and additionally, a chatbot will be developed and made available to complement the interventions on the other hand. This chatbot will answer specific questions of participants, for example, about symptoms or who to contact first, and it will also contain short psychological “learn”, “think”, “do”, exercises to improve participants well-being.

In the IG, a 3-day multidisciplinary *assessment* will be carried out promptly at a clinic to determine the individual need for treatment, the results of which are used as the basis for holistic treatment planning. Possible treatment recommendations are the initiation of rehabilitation, the provision of medical aids, specific therapies, the recommendation of digital health applications, and outpatient treatments.

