#### 3. Digital therapy offers

During the entire care process and after the onboarding performed by the personal pilots, digital intervention in terms of physical training courses and psychological interventions are provided to the patients. Patients can take part individually, regardless of location and time (so-called asynchronous offers [30]). The digital therapy services will support the treatment and bridge any waiting times for the patients in the IG to get the assessment and other therapies, as well as to support any indicated rehabilitation measures (cf. [33]). Patients in the IG will receive digital interventions on the basis of their physical resilience and patients in the ACG will receive one of three digital interventions based on their leading symptoms (fatigue, cardio-/respiratory, neuro-psychiatric).

In addition to the content of the digital tool, an interactive chatbot will be developed and tested during the duration of the ASAP project. The chatbot will focus more on short interventions targeting the management of symptoms in daily life, including self-discrepancies, pacing, and coping.

The patients will receive information and training to initiate the treatment of the present symptoms and to strengthen their self-management as well as to contribute to psychological stabilization. Contents include training in relaxation/breathing exercises, autogenic training, mindfulness/relaxation exercises, meditation, muscle relaxation as well as psychoeducation, strength training, physical endurance and coordination training, sensory training (including smell and taste), functional training as well as training on how to deal with the disease in an occupational context (cf. [34]).

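### Visits T3 to T5 are dated from the clinic assessment, so a patient randomised to the IG who does not attend it has no defined outcome measurement

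*Protocol article*

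**What the plan says.** The Evaluation concept section defines the visits. T1 is the screening. T2 and T3 fall "prior to the assessment in the IG and a comparable time point in the ACG (T2), after the assessment in the IG", and the wording for T3 in full is "after the assessment in the IG and at a comparable time point in the ACG (T3"). The later visits are chained to T3: "Then approximately 6 weeks after T3 and after symptom-specific digital interventions, a further measurement will take place (T4"), and "Another 6 weeks later a follow-up measurement will take place (T5"). T6 is for a selected subset only. No visit after T1 is given in weeks from randomisation or from screening.

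Under Comprehensive assessment program, the assessment is a 3-day inpatient stay, for the IG only, arranged after randomisation. The time to reach it is not stated. The Study design and setting section calls it prompt but gives no window, and says of the IG that "this unspecific digital intervention will be made available to bridge the time to an assessment that takes place in a clinic". The Digital therapy offers section likewise says the digital services will "bridge any waiting times for the patients in the IG to get the assessment".

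Two further statements bear on who is measured. If randomisation cannot be realised, for instance because the patient cannot take part in the assessment, the patient goes to the ACG and is marked for analysis. And the paragraph on the summative effectiveness evaluation describes endpoint collection from participants who completed the interventions.

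**The concern.** The outcome schedule in both arms starts from an event that follows randomisation and that only one arm can experience. An IG patient who cancels or stays away has no date after the assessment, so nothing fixes T3 or the two visits counted from it. An ACG patient has no assessment to miss.

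The wording on completed interventions points the same way. It could drop non-completers in either arm, but only the IG has a 3-day inpatient stay to get through. Some non-attendance is foreseeable: the evaluation plan itself intends to track attendance and drop-out.

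At stake are both primary endpoints, symptom reduction and return to work, in the only randomised comparison. Patients who stay away may be too impaired to travel, or may have recovered and gone back to work. These two possibilities push the IG result in opposite directions, so the sign of any bias cannot be predicted. Outcomes that were never collected cannot be restored by the analysis.

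A second, weaker issue is elapsed time. If the ACG date is not matched to the IG wait, the arms are compared at different times since randomisation in a condition that changes over time.

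**Working it through.** The plan gives no figure for the wait or for non-attendance, so there is no stated result to reproduce. The check is a reading of the visit rules plus simple arithmetic.

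**1. Visit dates for an IG patient who attends.** Let T3 fall w weeks after randomisation. Then T4 = w + 6 and T5 = w + 12. The values of w are assumed.

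| w (weeks) | T4 (weeks from randomisation) | T5 (weeks from randomisation) |
|---|---|---|
| 1 | 7 | 13 |
| 2 | 8 | 14 |
| 4 | 10 | 16 |
| 8 | 14 | 20 |
| 12 | 18 | 24 |

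Time since randomisation at T4 and T5 moves one-for-one with the wait.

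**2. Visit dates for an IG patient who does not attend.** There is no assessment, so w does not exist and T3, T4 and T5 have no date. T2 could still be taken if an appointment had been booked.

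**3. Does the fallback rule close the gap?** The Low-threshold online screening tool section says such patients are not randomly assigned; the Evaluation concept section sends them to the ACG when randomisation cannot be realised. Both describe patients for whom randomisation did not happen. Neither covers a patient allocated to the IG who later stays away. If the rule were applied after the dice roll, it would move IG non-attenders into the comparator, which is no better. On neither reading is such a patient kept in the IG with outcomes.

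**4. Difference in timing between arms.** Let the ACG's T3 fall c weeks after randomisation. The difference at T4 and T5 is (w + 6) − (c + 6) = w − c and (w + 12) − (c + 12) = w − c. If ACG dates are matched to IG waits, the mean difference is 0. If they are fixed, it is the mean wait minus c. The text does not say which applies.

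**5. Number of patients affected (assumed non-attendance 10–20%).**
- Planned IG size, Sample size planning section: 66. 0.10 × 66 = 6.6 and 0.20 × 66 = 13.2, about 7–13 patients.
- The dice rule (1–2 to IG, 3–6 to ACG) allocates 2/6 = 1/3 to the IG. With 132 randomised, 132 / 3 = 44. 0.10 × 44 = 4.4 and 0.20 × 44 = 8.8, about 4–9 patients.
- ACG patients lost for this reason: 0 in either case.

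**The case against.** The strongest reply is that no sentence says a non-attender goes unmeasured. Outcomes are online questionnaires filled in by the patient, so no clinic visit is needed. Personal pilots remind patients in both arms. The ACG already has a T3 without an assessment, so the design can date T3 for someone who was not assessed. Patients known to be unable to attend are kept out of the random allocation, which should reduce later non-attendance. Fig. 3, which is said to show all time points, is not visible, and a fuller protocol may add windows.

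Much of this shows that the gap is easy to close. It does not show that it is closed. The anchor is a stated choice, and visit windows around T3 would not by themselves create a T3 for someone with no assessment. The wording on completed interventions also works against assuming that everyone is followed.

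There is also a reasoned defence of the T3 anchor: each assessed IG patient is measured about 6 and 12 weeks after the assessment. That is a real advantage, and a fixed calendar gives some of it up.

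A reader might infer more than the text supports in two respects. The first is that the arms are in fact measured at different times since randomisation. The sentence defining the visits promises the ACG a comparable date at both T2 and T3, so the stated intention is the opposite, and any attempt to size a timing bias would rest wholly on assumptions and would have to include zero. The second is that the comparison group's lack of T2 and T3 dates harms the trial's main contrast. That group is not randomised, so its dates cannot bias the IG–ACG comparison.

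**Conclusion.** The point holds for non-attenders. As written, the visit definitions and the endpoint-collection sentence together leave a randomised IG patient who does not attend without a T3, T4 or T5 measurement, and loss by this route can occur only in the IG. The number affected is unknown: about 7–13 of 66, or about 4–9 of 44, if 10–20% do not attend. The direction of any resulting bias is not determined.

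On timing, the supportable conclusion is narrower. A comparable date is promised but not defined, and no visit is tied to randomisation, so elapsed time may differ by w − c, which is zero if dates are matched. The documents do not show that it does differ.

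Both conclusions are limited to the visible text, since Fig. 3 and any fuller protocol could add detail. The matter is worth correcting because it decides which outcomes are collected, but it does not by itself invalidate the design.

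**What to change.** - Schedule the T4 and T5 primary-outcome questionnaires at fixed weeks counted from randomisation, identical in the IG and ACG.
- Send them to every randomised patient, whether or not the assessment or the programme was completed.
- Amend the sentence on endpoint collection in the Evaluation concept section so that it no longer limits collection to participants who completed the interventions.
- State that patients are analysed in the arm to which they were randomised.
- T2 and T3 can stay around the assessment as process measures.

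The cost is protocol wording and a send-out calendar in the online survey tool that is already in use. The real downside is that an IG patient with a long wait will have had less of the tailored programme by the fixed visit.

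If the sponsor prefers to keep the T3 anchor for that reason, the minimum is to give IG non-attenders a T3 date by the same rule as the ACG, and to write down what that rule is.
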